**3c CHARACTERISTICS OF CENTERS**

The research is carried out in 2 hospital centers in Chile. These are HCUCH and CHSJ. The first corresponds to a private institution and the latter to a public institution. Patients hospitalized in the surgery, urology, and trauma wards of the HCUCH and the urology and trauma wards of the CHSJ will be included. The units serve people over 18 years of age, who require admission due to the evaluation of advanced studies, medical stabilization, and surgical interventions.

All centers have specialists, doctors, nurses, physical therapists, occupational therapists, and nursing technicians. The Non-Pharmacological Prevention of Delirium protocol will be implemented in all the selected wards.

**3d CHARACTERISTICS OF CARE PROVIDERS**

Each center has a specific coordinator and executing staff. All standard and experimental care providers will undergo training on "Delirium and Non-Pharmacological Prevention Measures”, and they will oversee the multidisciplinary research team (anesthetists, geriatrician, nurse, physical therapist, occupational therapists) which will be held 2 months before recruitment, to achieve a homogeneous standard treatment.

**4 INTERVENTIONS**

**4a PREPARATION OF LOCAL TEAMS TO IMPLEMENT A PROGRAM OF NON-PHARMACOLOGICAL PREVENTION OF DELIRIUM MEASURES IN THE CENTERS THAT WILL PARTICIPATE IN THE CLINICAL TRIAL.**

To carry out this design, a series of activities must be performed to ensure each of the key elements of the design. Preparatory activities for the process are described as follows:

- **Assess barriers and perceptions about the non-pharmacological prevention of POD:** in each of the 2 centers, the work team will carry out an initial evaluation of the barriers and perceptions about the non-pharmacological prevention of POD and, in this way, the next step will be planned, which is the training of the different clinical services of the centers that will care for the patients in our study. For this, we will use a questionnaire that has previously used and validated.
- **Standard non-drug prevention training for POD:** the clinical services that will receive the patients recruited in this study will be trained to implement the standard non-pharmacological preventive measures by the work team of this proposal. This training will allow patients in both groups to apply these delirium preventive measures, after which the effect of the preventive intervention performed by occupational therapists can be assessed.
- **Train the recruitment, intervention, and evaluation teams:** the work team will train each member of the study to carry out an activity. The study will have a team of health professionals for the recruitment and registration of clinical data; with a team of occupational therapists who will perform the non-pharmacological prevention intervention; and a team of healthcare professionals for evaluations that will include the diagnosis of delirium and the completion of the questionnaire to assess functionality.

**Study groups**

**Control group - Non-Pharmacological Prevention of Delirium:**

Standard non-pharmacological prevention of delirium: non-pharmacological strategies are the first-line approach in the prevention of delirium and this type of prevention is recommended by experts in hospitalized elderly adults. Currently, studies on the subject support education and training as an important prevention strategy. The following measures were implemented for our protocol (see Table 2):

1. **Reorientation protocol:** performed by the nursing team, consisting of directly informing the patient at least 3 times a day of the time, date, place, and reason for hospitalization.
2. **Early mobilization:** performed by a physical therapy team twice a day. It includes a sequence of passive and active mobilization of limbs, rolling and supine activation, supine to sitting transference, sitting, sitting to standing transference, walking in place, and ambulation.
3. **Sensory deficit correction**, it encourages the use of correctors and technical aids such as glasses, hearing aids, and dentures, among others. For this, the nursing team will request the necessary implements from the family upon admission to the hospital and the patient will be reminded daily of their use.
4. **Environmental management:** installation of a clock and other orientation elements in the patient´s room to promote orientation, in addition to minimizing environmental stressors.
5. **Sleep protocol:** lowering of lights, noise, and administration of nighttime drugs.
6. **Hydration protocol:** monitoring of the patient's hydration and access to it.
7. **Reduction of medication:** mainly anticholinergics and minimization of the use of benzodiazepines.

**Table 2. Summary of standard delirium prevention protocol**

| **Action** | **Procedure** | **Responsible** | **Frequency** | **Materials** | **Method of delivery** | **Record** |
| --- | --- | --- | --- | --- | --- | --- |
| **1. Reorientation protocol** | Directly inform the patient of the time, day, place, and reason for hospitalization. | Team of nurses | 3 times a day | Verbalization of team | Direct contact with the patient | It will be monitored by a team, on paper or using an intranet registration system |
| **2. Early mobilization** | Perform motor and respiratory exercises. | Physical therapy team | 2 times a day | Resistance Band | Direct contact with the patient, which will gradually be eased up according to the physical and medical conditions. |  |
| **3.Correction of sensory deficits** | Encourage the use of correctors and technical aids (glasses, hearing aids, dentures). | Team of nurses, family | 1 time per day | Diptych with material | Direct contact with the patient and family |  |
| **4. Management of environment** | Install clock and other orientation elements in the patient´s room. Minimize environmental stressors. Avoid using physical restraints, replacing them with the company of family members or another member of the team. | Team of nurses, healthcare team who is treating the patient, family members | 1 time per day | Paper  Marker  Glue | Direct contact with the patient |  |
| **5. Sleep protocol** | Train the team in reducing lights, noise and administration of drugs.  Promote night rest and daytime activation. | Team of nurses and family. | 1 time a day | Record sheet or clinical chart | Direct contact with the patient |  |
| **6. Hydration protocol** | Monitor patient hydration and check indications / availability. | Team of nurses | 2 times a day | Record sheet.  Clinical chart | Direct contact with the patient |  |
| **7. Decrease of medication** | Manage polypharmacy, decrease drugs with anticholinergic potential, and minimize the use of benzodiazepines. | Healthcare team who is treating the patient | 1 time a day | Record sheet.  Clinical chart | Review of clinical chart |  |

**Interventional group – Early and intensive Occupational Therapy**

Regarding OT intervention, specific training must also be carried out for the group of occupational therapists, to properly implement the OTs´ own strategies.

The OT intervention is implemented for 5 consecutive days, 2 times a day, in sessions before noon, and sessions after noon, and each session lasts 30 minutes.

The interventions to be carried out are grouped into the following 6 prevention areas (Table 3):

1. **Polysensory stimulation**: consisting of providing the patient with intense external stimulation regulated by different sensory channels (visual, auditory, tactile, proprioceptive and gustatory), with the objectives of increasing alertness, preventing sensory deprivation and increasing interaction of the patient with the objects and people around him/her (GES-ACV 2013 Clinical Guide recommendation).[(26)](https://paperpile.com/c/YGPhmB/mZ0v7) Sensory stimulation protocols have proven to be effective in other pathologies, such as states of minimal consciousness and dementia.[(27)](https://paperpile.com/c/YGPhmB/zBbzD) States that share some elements with delirium, therefore, can be used in patients with POD.
2. **Positioning:** consists of the early installation of orthosis and adaptations that leave areas with the highest frequency of bedsores free of pressure (sacral region, heels, among others). Proper positioning of the patient makes it possible to reduce the appearance of joint stiffness, which generates a positive impact on the patient's functionality in activities of daily living and, therefore, a reduction in the burden for health providers and their family.[(28)](https://paperpile.com/c/YGPhmB/cxK4s) They also reduce the appearance of pressure ulcers, one of the conditions that causes longer hospital stays and higher costs, and finally, it allows to provide comfort to the patient during hospitalization.
3. **Cognitive stimulation**: intervention aimed at keeping mental functions active. According to the International Classification of Functionality these are: consciousness, orientation, attention, memory, calculation, praxis and language, which are included in 6 areas of action: i) attention and wakefulness, ii) visual perception, iii) memory, iv) calculation and problem solving, v) praxis and vi) language.[(22)](https://paperpile.com/c/YGPhmB/b8oXl)
4. **Basic Training in** **Activities of Daily Living (ADL)**: The intervention will focus on encouraging ADL such as hygiene, grooming and nutrition performed independently. There are many benefits of ADL training in hospitalized elderly adults. These allow to structure their time (generating daily routines that favor the maintenance of habits), maintain their independence (functional maintenance in the daily activities of the elderly person prevents and reduces their physical, psychological, and social deterioration) and promote the feeling of usefulness. Each patient must maintain a daily routine of activities of daily living with times for cleaning, hygiene, breakfast, lunch, tea, and dinner, in a normal environment (sitting on the side of the bed or out of bed). Independent performance will be encouraged, and the occupational therapist, nurse, nursing technician or family member will only be a guide for the safe execution of the activity.[(29,30)](https://paperpile.com/c/YGPhmB/lzCp2+rTuII) Information will be provided to family members with the necessary recommendations.
5. **Motor stimulation of upper limbs:** it consists of maintaining or activating functional movements and the strength of the upper extremities, through the performance of movements towards the midline with the use of objects, bimanual coordination, ergotherapies, prehensions, writing and use of therapeutic tools. The motor stimulation of upper extremities will be used as the necessary baseline for the optimal performance of the ADL, since it has been documented that the grip force is a good predictor of independence in the ADL, cognitive status and mortality in elderly people.[(31)](https://paperpile.com/c/YGPhmB/zWD7r)
6. **Participation of family:** the incorporation of the family in health interventions, particularly with the elderly, is a feasible and effective resource, as reported in some studies.[(32)](https://paperpile.com/c/YGPhmB/BTGi6) Therefore, their participation in this intervention is essential. It will begin with the identification of the family members who will collaborate with the intervention, who will be given information detailing their specific role. Likewise, they will be asked for material to work with, such as photographs or other significant elements for the elderly person.

**5 OUTCOMES**

**Primary outcome**

Incidence of POD and PODS: Two evaluations will be performed per day with CAM for five consecutive days

**Secondary outcome**

- *DURATION OF POD AND PODS*. Two evaluations will be performed per day with CAM for five consecutive days.
- *MORTALITY.*
- *HOSPITAL STAY.*
- *FUNCTIONAL ASSESSMENT*, considers independence with FIM, cognitive status with MMSE, and grip strength with dynamometry.
- In addition, socio-demographic data, and clinical information (reason for admission, Charlson Comorbidity Index) will be collected.

**Assessment of primary outcome:**

INCIDENCE OF POSTOPERATIVE DELIRIUM (POD) AND POSTOPERATIVE SUBSYNDROMAL DELIRIUM (PODS). Confusion Assessment Method (CAM) was developed in 1988-1990, to improve the identification and recognition of delirium.^10^ CAM was intended to provide a new standardized method to enable non-psychiatrically trained clinicians to identify delirium quickly and accurately in both clinical and research settings. The CAM had a sensitivity of 94% (95% CI 91-97%) and specificity of 89% (95% CI 85-94%).[(33)](https://paperpile.com/c/YGPhmB/6osiQ) Generally, the entire CAM rating takes 5-10 minutes to complete.

Delirium incidence will be assessed using CAM, applied by a trained occupational therapist twice a day during the first 5 days of hospitalization including weekends. CAM positive diagnostic criteria is fulfilled by the presence of (1) Either acute change or fluctuation, obtained from a family member or nurse aware of the patient’s baseline mental status, and (2) Inattention assessed by difficulty focusing attention during conversation (being easily distractible or having difficulty keeping track of what was being said) or wrong attentional tests, plus either (3) Disorganized or incoherent thinking, defined as rambling or irrelevant conversation, unclear or illogical flow or of ideas, unpredictable switching from subject to subject during patient assessment, or (4) An altered level of consciousness defined as vigilant, lethargic, stupor or coma. The attentional tests used are month of the year or days of the week backwards, digit-span backwards (4 digits) or A test.

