**3 METHODS AND PROCEDURES**

**3a TRIAL DESIGN**

A randomized clinical trial (RCT) is proposed with a multicenter prospective, with parallel groups, in a 1:1 ratio, in 2 Chilean hospitals. The records will be made at the beginning of the study, during the interventions, and at hospital discharge.

For RCT planning, the CONSORT[(23)](https://paperpile.com/c/YGPhmB/4F2IU) methodological recommendations for reporting non-pharmacological trials are used, in addition to the TIDieR[(24)](https://paperpile.com/c/YGPhmB/ZcWDA) and SPIRIT standards.[(25)](https://paperpile.com/c/YGPhmB/FtlaA)

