**6 SAMPLE SIZE**

It was calculated based on the primary outcome, which is the development of POD in the first 5 postoperative days or until discharge, whichever occurs first. In a previous study carried out at HCUCH, it was found that 21% of patients > 75 years of age presented POD in the first 5 postoperative days (unpublished data, presented at the Chilean Congress of Anesthesiology 2016). Furthermore, it was determined by our group that preventive therapy performed by occupational therapists decreased the incidence of delirium in patients hospitalized in the Critical Patient Unit of said hospital from 20% to 3%.[(22)](https://paperpile.com/c/YGPhmB/b8oXl) So, to detect an absolute decrease of 15% in the incidence of POD (from 20% in Group Control to 5% in Group Interventional), with a power of 80% and a two-tailed of 0.05, and considering a 10% loss in the follow-up of the patients, 80 patients per group should be studied. Therefore, 160 subjects must be recruited from patients > 75 years who underwent highly complex elective surgery.

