**12 STATISTICAL METHODS**

The data will be acquired both on paper and in an electronic database. However, to maintain the confidentiality of patients in the electronic database, only the recruitment code will be recorded and not the names. The recorded data will be analyzed by the researchers blind to the therapy. The primary outcome of this analysis will be to determine the incidence of POD and PODS at any time postoperatively, as previously defined. This analysis will allow us to establish whether a therapy performed by occupational therapists significantly reduces the incidence of POD. In addition, this analysis will have as secondary objectives to determine if the intervention by occupational therapists reduces the severity and duration of POD, and if it improves the functionality of the patients on the 5^th^ postoperative day.

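### The CAM rule counts the primary-outcome window from hospitalisation, while the outcome definition behind the sample size counts it from surgery

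*Protocol*

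**What the plan says.** The protocol describes the primary-outcome window in several places:

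- Section 5, Assessment of primary outcome, is the only instruction on when the CAM is applied for this outcome that names a starting event: "twice a day during the first 5 days of hospitalization including weekends".
- Section 6 says the primary outcome is "the development of POD in the first 5 postoperative days or until discharge, whichever occurs first". It cites an incidence of 21% over the first five postoperative days from an earlier study at one of the two hospitals, and plans on a control rate of 20%.
- Section 2b, first specific objective, also refers to the first five postoperative days.
- Section 5, Primary outcome, says "Two evaluations will be performed per day with CAM for five consecutive days". The secondary-outcome list and the duration-of-delirium entry likewise give five consecutive days. None of them names the day on which counting starts.
- Section 12 says the analysis will determine "the incidence of POD and PODS at any time postoperatively, as previously defined".

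Table 1 excludes delirium found by CAM at admission or before the intervention starts. No section gives a length of preoperative stay or says on which day, relative to surgery, the CAM series begins.

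**The concern.** Hospitalisation and surgery are different events, and they can fall on different days. The summary describes participants as admitted patients who are going to have surgery. Table 1 separates delirium at admission from delirium before the intervention starts, which allows for a gap between the two. An evaluator who follows the Section 5 instruction for such a patient starts counting at admission and stops before the fifth postoperative day. Section 2a says delirium after surgery arises during the first week, so events can fall in the days that are dropped.

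Two things are at stake. The incidence observed would not be the quantity for which 20% was assumed. And because the window governs bedside data collection, an assessment not made on postoperative day 4 or 5 cannot be recovered at analysis, so an analysis plan cannot repair it. The status of a patient discharged early also depends on the sentence followed: Section 6 ends the window at discharge, and Section 5 is silent.

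**Working it through.** **1. The plan's own figure.** Inputs, all from Section 6 except the allocation ratio: "from 20% in Group Control to 5% in Group Interventional"; "with a power of 80% and a two-tailed of 0.05"; "considering a 10% loss in the follow-up of the patients"; and from Section 3a, "with parallel groups, in a 1:1 ratio".

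Unpooled normal approximation, per group: n = [p1(1−p1) + p2(1−p2)] × (1.960 + 0.842)² / (p1−p2)² = (0.1600 + 0.0475) × 7.849 / 0.0225 = 72.4, so 73. Allowing for loss: 73/0.90 = 81.1, so 82; or 73 × 1.10 = 80.3, so 81. The arcsine formula gives 70, then 70/0.90 = 77.8, so 78. The pooled formula gives 76, then 85 (98 with continuity correction). The stated 80 per group is within two patients of the first two methods, so no numerical error is raised. The calculation rests on the postoperative window.

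**2. The two windows side by side.** Suppose a patient is admitted k days before surgery. Surgery then falls on hospital day k+1, and hospital day 5 is 4−k days after surgery.

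| Admission | Postoperative days lost if surgery is day 0 | Lost if surgery is postoperative day 1 |
| --- | --- | --- |
| Day of surgery (k = 0) | 1 (day 5) | 0 |
| One day before (k = 1) | 2 | 1 |
| Two days before (k = 2) | 3 | 2 |

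The planned series is 2 × 5 = 10 assessments, so each full preoperative day uses 2 of 10, or 20%. The windows agree only for same-day admission with the day of surgery counted as postoperative day 1. The protocol states neither condition.

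**3. Do the other passages settle it?** The five-consecutive-days statements fit either start. Section 12 refers back to an earlier definition, but the two earlier ones conflict. Sections 2b and 6, and the outcome's name, favour the postoperative window. That makes the CAM instruction the likely outlier, but it is the sentence that evaluators would follow.

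**4. Illustration of the effect on power.** Evaluable per arm: 80 × 0.90 = 72. With d = p1−p2 and p̄ the mean of the two rates, power = Φ{[d√n − 1.960√(2p̄(1−p̄))] / √(p1(1−p1) + p2(1−p2))}.

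Assumptions that are not in the protocol: onset is spread evenly over postoperative days 1 to 5, and every patient in both arms loses the same number of days.

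- None lost, 20% v 5%: (1.273 − 0.917)/0.4555 = 0.782, power 78%.
- One lost, 16% v 4%: (1.018 − 0.832)/0.4157 = 0.449, power 67%.
- Two lost, 12% v 3%: (0.764 − 0.730)/0.3670 = 0.092, power 54%.
- Three lost, 8% v 2%: (0.509 − 0.604)/0.3053 = −0.311, power 38%.

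The onset pattern matters because days are lost from the end of the window. If only 10% of onsets fell in the lost days (also an assumption), the rates would be 18% v 4.5%: (1.146 − 0.876)/0.4365 = 0.618, power 73%.

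**The case against.** The best defence is that the intent is clear. The outcome is named postoperative delirium, the CAM paragraph is headed as assessing it, and Sections 2b and 6 agree on five postoperative days, so a sensible team would start after surgery. With same-day admission, at most the fifth postoperative day is lost. This stands as a limit on the size of the problem. It does not remove the contradiction, because the only CAM instruction with a starting event names the wrong one.

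A reader might infer more than the protocol supports:

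- **Three competing windows.** Section 12 sounds open-ended, but it ties itself to what was defined before. It is loose wording and not an independent third window.
- **Preoperative delirium counted as an event.** Section 2a defines the condition as occurring after surgery, and Table 1 excludes delirium before the intervention. Early assessments would waste window days; under these definitions they should not add events.
- **A difference between hospitals or a bias between arms.** Nothing is said about admission practice at either hospital. Randomisation is separate by centre, so preoperative stay should be similar across arms. The supported harm is missed events.
- **A known loss of power.** The figures need an assumed onset pattern and an assumed loss for every patient. They show sensitivity and do not predict this trial's power.

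**Conclusion.** Wrong as written. The CAM instruction in Section 5 and the outcome definition in Section 6 start the primary-outcome window at different events, and no other passage resolves the conflict. This rests on the text alone and is firm. It is a misstated rule and not a detail left for an analysis plan.

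The consequence is conditional. Late postoperative days go unassessed for patients admitted at least a day before surgery, and possibly day 5 for same-day admissions, depending on day numbering. Because the protocol gives neither preoperative stay nor daily risk, the number of missed events cannot be computed. The illustrated range, from 78% down to 67% or 54% for one or two days lost by everyone, holds only under its stated assumptions; a late-light onset pattern would cost less. The sample size is unaffected, since it already uses the postoperative window.

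**What to change.** - In Section 5, Assessment of primary outcome, replace the window counted from hospitalisation with the one in Section 6: five postoperative days, or to discharge if earlier.
- Tie the five-consecutive-days statements in Section 5 (primary outcome, secondary outcomes, duration of delirium) and the incidence sentence in Section 12 to that same window.
- State explicitly whether the day of surgery counts. Section 6 does not say, and Section 2a recommends looking for delirium as early as the recovery unit. A start on the day after surgery should therefore not be read into Section 6; the sponsor has to decide.
- Use any preoperative CAM only for the Table 1 exclusion.

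The cost is wording and a note to the evaluators. Five days at two assessments a day remain ten at most, and the target stays at 80 per group, 160 in total.
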